### Outcome measures

Measures related to the primary aim (i.e. feasibility and tolerance) will be recorded throughout the duration of the study using exercise logs and scheduled contact points with the participants. Assessments related to the secondary aim and those used to evaluate the PRP will be performed at three time points: (i) prior to randomisation (i.e. at baseline), (ii) on completion of the 8-week PRP (interim assessment) and (iii) on completion of the 40-week intervention period. During these assessment periods, measures will be made (across two non-consecutive days) of BMD, body composition, balance, falls risk, exercise capacity, HRQoL, functional limitation resulting from dyspnea and feelings of anxiety and depression. In addition, descriptive variables including height, weight, age, gender, lung volumes and smoking history will be recorded. Specific details on the measures and assessments are provided below. Body composition and BMD will only be measured at two time points, at baseline and on completion of the 40-week intervention period.

### Primary outcomes

#### Feasibility

To assess feasibility of the study protocol, data will be recorded pertaining to recruitment, withdrawal and completion, as well as adherence to the prescribed sessions (Table 2). The following cut-off points will be used to determine feasibility: recruitment rate of 50% (of participants screened as eligible for the study) and completion rate of 70% (including all assessments and intervention period). Adherence to all exercises prescribed during the PRP and at home will be tracked using exercise logs, completed by the participant. A completion rate of 75% of supervised and home-based exercises will be considered adherent to the intervention.

**Table 2 Tab2:** Measures to assess feasibility of the impact loading exercise

Recruitment and completion	- Number of participants who were screened - Number of eligible participants who were recruited (i.e. provided written consent) - Number of participants who withdrew - Number of participants who completed the intervention period - Number of participants who completed all assessments and the intervention period
Adherence	- Number of supervised sessions completed - Number of home-based sessions completed

#### Tolerance

Tolerance of the experimental intervention will be compared to the standard PRP by:Asking participants to rate any lower limb joint discomfort/pain at the completion of each exercise component of the exercise programme through use of the visual analogue scale (VAS; 0 to 10) [35]. These components include the walking programme, upper and lower limb resistance exercises and for the experimental group the targeted high-intensity lower limb resistance and impact loading exercises. During the home-based sessions, participants will be asked to record the VAS score for pain in a workbook and to contact the research team for guidance if they experience any increase in pain. Rating of perceived exertion (RPE) will be recorded using the RPE scale and breathlessness using the modified BORG dyspnoea scale [36].Asking participants to immediately contact the primary investigator if they experience any adverse events, such as a fall, throughout the duration of the study. These data will be recorded by the primary investigator.On study completion, feedback regarding their experiences will be sought from the participants, in the experimental group only, through semi-structured interviews.

### Secondary outcomes

#### Bone mineral density and body composition

Dual-energy X-ray absorptiometry (DXA, Lunar Prodigy) will be used to assess BMD (g/cm^2^) of the hip (total hip and femoral neck) and lumbar spine (L2 to L4) regions as well as whole body bone mineral content (BMC, g) and body composition. Regional and whole body lean mass (including appendicular skeletal muscle mass) and fat mass will be derived from the whole body DXA scan. The DXA scan will be conducted by a trained technician who will be blind to group allocation.

#### Balance

Balance will be assessed using the Berg Balance Scale (BBS) and the Four Square Step Test (FSST). The BBS is one of the most widely used clinical outcome measures to assess balance in older adults and has been shown to be sensitive to change following completion of a PRP in people with COPD [37, 38]. The FSST measures dynamic balance and is a reliable and valid measure for predicting falls in the elderly [39]. In addition the Activities-specific Balance Confidence (ABC) questionnaire will be used to determine participant’s confidence in performing activities without losing their balance and has good test–retest reliability and predictive capacity for falls in adults living in the community [40, 41].

#### Falls risk

Falls risk will be screened using the Falls Risk for Older People in the Community Screen (FROP-Com Screen). This is a 3-item falls risk screening tool that includes falls history in the past 12 months, functional status and balance. The score ranges between 0 and 9 and scores ≥ 4 indicate high risk of falls [42].

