### Experimental intervention

In addition to the standard PRP, over the initial 8-week period, participants allocated to the experimental group will also undertake additional targeted, lower limb resistance exercises and commence a programme of impact loading exercise. The resistance exercises will be commenced at the beginning of the 8-week PRP and are designed to improve gluteal, hamstring, quadriceps and calf muscle strength in preparation for the impact loading exercises. The impact loading exercise will commence in week 5 of the PRP and will be undertaken in accordance with current recommendations on exercise prescription for the prevention and management of osteoporosis [21]. Details of the exercises including type, sets and repetitions are included in Table 1. The intensity, frequency, number of sets and repetitions of each impact loading exercise will be tailored taking into account the participant’s existing bone health status, co-morbidities and functional/clinical risk factors for falls and fractures. Each participant will be categorised as low, moderate or high risk for a fragility fracture and the prescription of the impact loading exercises will be modified accordingly [21]. The exercises will be modified as required, taking into account the participants physical capabilities and/or any reports of pain. All modifications to the exercises will be recorded in the exercise training logs.

**Table 1 Tab1:** Progression and prescription of impact loading exercise

	**Phase 0**	**Block 1**	**Block 2**	**Block 3**	**Block 4**
**Weeks**	1–4	5–8	9–16	17–28	29–40
**Impact loading exercises**	N/A	- Bounding over soft hurdles (13–16 cm); 10 times - Drop Jumping (10–15 cm); 10 times	- Same as Block 1	- Bounding over soft hurdles (13–16 cm); 10 times - Drop Jumping (10–15 cm); 10 times - Hopping on one leg; 10 times	- Bounding over soft hurdles (13–16 cm); 10 times - Drop Jumping (10–15 cm); 10 times - Hopping on one leg; 10 times - Leaping; 10 times
**Number of rotation and rest between sets**	N/A	- Two rotations and 1–2-min rest between sets	- Three rotations and 1–2-min rest between sets	- Three rotations and 1–2-min rest between sets	- Three rotations and 1–2-min rest between sets
**Frequency**	N/A	- Weeks 5 and 6 twice weekly (supervised) - Weeks 7 and 8 twice weekly (supervised) and twice weekly (unsupervised)	- Four times weekly (home-based)	- Four times weekly (home-based)	- Four times weekly (home-based)

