### Data management and analyses

Data will be entered and stored using REDCap data collection tools [33]. All data from the REDCap database will be de-identified. Statistical analyses will be performed using SPSS® (Statistical Package for Social Sciences, version 25.0 for Windows). As this is a pilot study, data pertaining to the primary aims (i.e. feasibility/tolerance) will be reported using descriptive statistics such as means and standard deviations (parametric data) or medians and interquartile ranges (non-parametric or ordinal data). Categorical data will be reported as frequencies and proportions. Estimates of the effect of the intervention on bone health, balance and falls risk will be determined using linear regression analysis and unstandardised beta coefficients.

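### The falls-history item of the falls-risk outcome looks back 12 months, so part of its window at week 40 (23%) and most at week 8 (85%) precedes randomisation, which attenuates any effect carried by that item

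*Protocol article*

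**What the plan says.** Study aim(s) in the protocol article includes reporting the effect of the added exercise on falls risk. The Falls risk section names one instrument, the FROP-Com Screen, and describes it: "This is a 3-item falls risk screening tool that includes falls history in the past 12 months, functional status and balance". On scoring it says only: "The score ranges between 0 and 9 and scores ≥ 4 indicate high risk of falls". It gives neither the weight of each item nor a shorter recall period for follow-up.

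Outcome measures lists falls risk among the assessments made at baseline and then "ii) on completion of the 8-week PRP (interim assessment) and (iii) on completion of the 40-week intervention period". The only outcomes exempted from the week-8 visit are these: "Body composition and BMD will only be measured at two time points, at baseline and on completion of the 40-week intervention period". Falls risk is therefore scored at both follow-ups.

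Data management and analyses then states: "Estimates of the effect of the intervention on bone health, balance and falls risk will be determined using linear regression analysis and unstandardised beta coefficients". The Abstract (Methods) ties the reported effects on bone health, balance and falls risk to the full 40-week intervention.

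**The concern.** A 12-month look-back suits a baseline screen. As a follow-up measure taken less than 12 months after randomisation, it mixes falls from before and after treatment began. A participant who fell shortly before baseline still has that fall counted at 8 and 40 weeks, whatever the intervention does.

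The Discussion says the effect sizes for bone mineral density, balance and falls risk are critical to the design of a definitive trial. A falls-risk coefficient that is partly damped by the instrument's window is a poor input for that purpose. The damping also differs between visits, so an apparent growth in effect from week 8 to week 40 could come partly from the window itself.

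**Working it through.** The plan gives no figure for falls risk to reproduce. Its sample size is justified on bone mineral density and is not affected by this point.

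**Inputs from the protocol article**
- Look-back of the falls item: 12 months, taken as 52 weeks (Falls risk).
- Follow-up visits: w = 8 and w = 40 weeks (Outcome measures), counted as if the programme starts at randomisation. Any gap before it starts lowers the pre-randomisation shares slightly.
- 12-month prevalence of falls in COPD: 40% (Background), used only for the illustration at the end.

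**Assumption.** A true fall-rate ratio RR acts from randomisation onward, on an otherwise constant fall rate. The documents give no value, so a range of 0.5 to 0.7 is shown.

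**Formulas**
- Share of the window before randomisation = (52 − w)/52.
- Fall-rate ratio seen over the whole window = (52 − w)/52 + (w/52) × RR.

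| | Week 8 (interim) | Week 40 |
|---|---|---|
| Share before randomisation | 44/52 = 84.6% | 12/52 = 23.1% |
| Apparent ratio, RR = 0.5 | (44 + 4)/52 = 0.92 | (12 + 20)/52 = 0.62 |
| Apparent ratio, RR = 0.7 | (44 + 5.6)/52 = 0.95 | (12 + 28)/52 = 0.77 |

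**Exposure to impact loading itself.** The article states: "The impact loading exercise will commence in week 5 of the PRP". About 4 of the 52 weeks (7.7%) follow its start at week 8, and about 36 of 52 (69.2%) at week 40. The added resistance exercises start earlier, at the beginning of the programme, so the table's assumption of an effect from randomisation is a simplification that favours the plan.

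**Illustration as the proportion with at least one fall in the window.** With Poisson falls, a 40% annual prevalence gives a rate of −ln(1 − 0.40) = 0.511 per year. Let r be the apparent ratio from the table, or RR itself for a window wholly after randomisation. The experimental-arm proportion is 1 − exp(−0.511 × r), against 40% in controls.
- RR = 0.5: 37.6% at week 8 (difference 2.4 points) and 27.0% at week 40 (13.0 points). A full 12-month window after randomisation would give 22.5% (17.5 points).
- RR = 0.7: 38.6% at week 8 (1.4 points) and 32.5% at week 40 (7.5 points), against 30.1% (9.9 points).

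**What cannot be computed.** The planned analysis is a linear-regression coefficient on a 0 to 9 score. The article states neither how falls convert to points nor how much weight the item has, so the figures above describe the falls in the window and not that coefficient.

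**The case against.** The case for leaving the plan alone has several sound parts.

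- **Week 40 is the visit that matters.** Week 8 is labelled interim, and the Abstract points to the 40-week effect. At week 40, 40/52 (77%) of the window follows randomisation. At week 8 there have been only about four weeks of impact loading, so little effect on falls would be visible with any recall period. This stands, and the 23% figure should lead.
- **Only one item of three has the look-back.** No window is stated for function and balance, and both can respond at either visit. Past falls are also a legitimate part of a risk score. This stands.
- **Randomisation balances earlier falls in expectation.** This stands: neither arm is favoured. Adjusting for baseline would remove some noise, but it would not restore the effect lost to the window.
- **Falls are already recorded as adverse events.** This stands only in part. They serve tolerance, and they depend on participants reporting them. The experimental arm is phoned fortnightly and controls every 4 weeks, and the questions listed for the control calls do not mention falls. Relying on these records alone could replace even dilution with unequal ascertainment.

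A reader might infer that the score cannot register any effect on falls at 8 weeks, that the whole falls-risk outcome mostly counts old falls, or that a third of its points are affected. The documents support none of these. Eight of the 52 weeks do count at week 8, two items are untouched by the look-back, and item weights are not given.

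**Conclusion.** The point holds as attenuation of one component of a secondary outcome. At week 40, 23% of the falls item's window precedes randomisation; at the interim visit, 85% does. Under an assumed constant true rate ratio of 0.5 to 0.7, the item's window would show about 0.62 to 0.77 at week 40 and 0.92 to 0.95 at week 8. That difference between visits would arise with no change in the true effect.

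The window shares rest only on the instrument and visit times fixed in the article, so no modelling choice in an analysis plan would alter them. The apparent ratios also rest on the assumed effect size, its onset at randomisation and a constant underlying fall rate. The size of the effect on the total score remains unknown. The feasibility and tolerance outcomes are not affected. The change is worth making because the falls-risk estimate is meant to inform a larger trial and the remedy is cheap.

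**What to change.** 1. Keep the standard FROP-Com total as planned, so that it stays comparable with its cut-off of 4. Name week 40 as the main falls-risk contrast.
2. Also report the function and balance items separately from the falls-history item, by arm and visit.
3. Add falls since randomisation by arm, as falls per person-time and as the proportion with at least one fall. Collect them with the same question in both arms at the existing week-8 and week-40 assessments. Do not rely only on the adverse-event calls.
4. Do not rescore the falls item over the time since randomisation. Its windows would then be 52, 8 and 40 weeks at the three visits, so the item would tend to fall from baseline in both arms merely because the window is shorter, and the cut-off would no longer apply.

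The cost is one added question at visits already scheduled and a small descriptive table. The new count will carry some recall error, most of all over the longer interval to week 40.

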### Outcomes completed as part of the usual pulmonary rehabilitation programme

Other outcomes completed as part of the standard PRP will include the following: exercise capacity, measured using the 6-min walk test (6MWT) [43, 44]; HRQoL, measured using the interviewer administered version of the Chronic Respiratory Disease Questionnaire (CRDQ) [45]; functional limitation resulting from dyspnoea using the modified Medical Research Council Scale (mMRC) [46]; and anxiety and depression using the Hospital Anxiety and Depression Scale (HADS) [47, 48].

### Data management and analyses

Data will be entered and stored using REDCap data collection tools [33]. All data from the REDCap database will be de-identified. Statistical analyses will be performed using SPSS® (Statistical Package for Social Sciences, version 25.0 for Windows). As this is a pilot study, data pertaining to the primary aims (i.e. feasibility/tolerance) will be reported using descriptive statistics such as means and standard deviations (parametric data) or medians and interquartile ranges (non-parametric or ordinal data). Categorical data will be reported as frequencies and proportions. Estimates of the effect of the intervention on bone health, balance and falls risk will be determined using linear regression analysis and unstandardised beta coefficients.

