**Targeted lower-limb resistance exercises (In PR only, twice weekly)**	Calf raises, Knee flexion and extensions with multi gym, Seated hamstring curls with theraband if unable to complete knee flexion with multi gym, squats and lunges; 1–3 sets of 8–10 reps	- Same as phase 0	N/A	N/A	N/A
**Further Details**	Pulmonary rehabilitation only	- The first home-based session of this block will be supervised by a study investigator	- Home-based impact loading exercises will be the same as Block 1	- The first home-based session of this block will be supervised by a study investigator due to the progression of the impact loading exercise progression	- The first home-based session of this block will be supervised by a study investigator due to the progression of the impact loading exercise progression

The additional exercises will be closely supervised by a physiotherapist and implemented within the standard PRP using a circuit training approach. Those who tolerate the impact loading exercises well during weeks 5 and 6 of the PRP, with no reports of pain and no safety concerns, will be asked to complete an extra two sessions of home-based impact loading exercise in weeks 7 and 8. The first home-based session will be supervised by a physiotherapist. A suitable area will be established in the patient’s home environment to complete the exercises taking into account safety as well as a consistent floor surface. Participants will also be asked to wear the same or similar footwear every time they complete the exercises. In those who describe difficulties with the impact loading exercise in week 6 of the PRP, such as onset of pain or intolerable breathlessness, home-based training will be delayed until such time as they report no difficulties. Individuals who report issues with continence whilst performing the impact loading exercises will be offered a referral to a continence physiotherapy clinic. If difficulties during impact loading exercise are reported up to week 8, the individual’s participation in the intervention will be discontinued, but they will be asked to attend all remaining assessment sessions so their data can be analysed according to the intention to treat principle.

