### Sample size calculations

Justification of the sample size for pilot studies needs to balance issues of imprecision (small samples) against cost (large samples). As the primary goal of the pilot study is determining feasibility outcomes and not ensuring adequate power to detect a small between-group difference, it is inappropriate to calculate the sample size required to detect between-group differences. For this study, justification of the sample size aligns with an approach that has been described by experts that utilises confidence intervals (CI) [49]. The sample size will be large enough to provide a level of precision around an estimate of the effect for a given outcome (e.g. between-group difference in BMD) that would indicate that a definitive RCT in this area is worth pursuing. Rather than the usual 95% CI required for hypothesis testing, experts suggest that an 80% CI will satisfy the need for reasonable certainty for decision making based on pilot data. Using this approach, a sample size of 46 will allow us to comment on whether a standardised effect size for the change in BMD of 0.25 would be considered realistic in a definitive RCT. To account for a predicted 20% drop out rate, the target sample size for the study will be 58. In the previous annual report for 2017/2018, 222 people with COPD were referred to the pulmonary rehabilitation programme at St John of God Midland Hospital, a significant increase from the 138 patients referred the year before (2016/217). Of these, 81 were enrolled in the programme. We anticipate there will be a sufficient number of referrals to the programme to recruit 58 participants over a 2-year period.

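### Balance and falls risk are measured at three visits with 20% drop-out predicted, but the named linear regression, unless combined with imputation, leaves unused the week-8 data of people lost before week 40

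*Protocol article*

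**What the plan says.** All references are to the protocol article.

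- **Visits (Outcome measures).** "Assessments related to the secondary aim and those used to evaluate the PRP will be performed at three time points": baseline, the end of the 8-week programme, and week 40. Balance and falls risk follow this schedule. Bone density does not: "Body composition and BMD will only be measured at two time points, at baseline and on completion of the 40-week intervention period".
- **Method (Data management and analyses).** "Estimates of the effect of the intervention on bone health, balance and falls risk will be determined using linear regression analysis". One method is named for all three domains. The article does not say which visit supplies the outcome, whether week 8 enters the model, or what happens to missing values.
- **Drop-out (Sample size calculations).** "To account for a predicted 20% drop out rate, the target sample size for the study will be 58".
- **Intention to treat (Experimental intervention).** For participants whose intervention is discontinued because of difficulties up to week 8: "they will be asked to attend all remaining assessment sessions so their data can be analysed according to the intention to treat principle".

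The primary aims, feasibility and tolerance, are reported descriptively. The effects on bone health, balance and falls risk belong to the secondary aim, although the Discussion treats them as critical input to a definitive trial.

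**The concern.** For balance and falls risk there are two correlated follow-up values per person, and the named method uses one. Someone seen at week 8 but not at week 40 contributes nothing to a week-40 regression on observed values, although the week-8 result is the best available evidence on how that person was doing.

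This matters if loss after week 8 is related to week-8 status differently in the two arms. The design makes that plausible. Impact loading starts in week 5, in the experimental arm only, and continuing difficulties up to week 8 end participation in it. After week 8, phone contact is fortnightly in the experimental arm and four-weekly in controls. If people doing worse at week 8 are lost selectively from the experimental arm, the remaining experimental participants are compared with an unselected control group, and the contrast favours the intervention. An optimistic estimate could then carry into the planning of the next trial.

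**Working it through.** **1. The plan's own figures.** The inputs are an analysable sample of 46, a standardised effect of 0.25 for BMD change, an 80% CI, 1:1 allocation and 20% drop-out. The half-width of a CI for a standardised mean difference is z × √(4/N). The article does not state sidedness; the one-sided 80% value, z = 0.842, reproduces its figure:

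- N = 4 × (0.842/0.25)² = 45.4, rounded up to 46. The half-width at 46 is 0.842 × √(4/46) = 0.248.
- 46/0.8 = 57.5, rounded up to 58.
- 58 × 0.8 = 46.4, so about 46 people are expected at week 40 and about 12 are not.

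**2. The two estimators.** Write y0, y8 and y40 for the three visits.

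- *Week-40 regression on those present:* regress y40 on arm and y0, and take the arm coefficient.
- *Likelihood estimate using week 8:* regress y8 on arm and y0 in everyone (arm coefficient a). Regress y40 on arm, y0 and y8 in those present at week 40 (arm coefficient c, y8 coefficient d). The week-40 effect is c + d × a.

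**3. Assumptions.** The documents give no visit correlations and no pattern of loss, so both are assumed. Outcomes have SD 1, higher is better, with 29 per arm and about 20% loss overall. Positive bias favours the experimental arm; it would change sign if those doing better were the ones lost.

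**4. Simulation A.** The true week-40 effect is 0.25 SD, all visits are equally correlated, and there are 6,000 trials per row. Loss is random, or related to the week-8 score by the same logistic rule in both arms, or strongly related to it in the experimental arm only.

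| Correlation | Loss | Bias, regression | SD | Bias, with week 8 | SD |
|---|---|---|---|---|---|
| 0.5 | random | −0.002 | 0.259 | −0.001 | 0.257 |
| 0.5 | both arms | −0.002 | 0.259 | 0.002 | 0.257 |
| 0.5 | experimental only | 0.059 | 0.258 | 0.000 | 0.258 |
| 0.7 | random | −0.003 | 0.214 | −0.002 | 0.210 |
| 0.7 | both arms | −0.001 | 0.211 | 0.001 | 0.209 |
| 0.7 | experimental only | 0.050 | 0.214 | 0.000 | 0.212 |
| 0.8 | random | 0.000 | 0.180 | −0.001 | 0.176 |
| 0.8 | both arms | 0.001 | 0.179 | 0.003 | 0.177 |
| 0.8 | experimental only | 0.039 | 0.183 | 0.000 | 0.180 |

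**5. Simulation B.** The true effect is 0, with 6,000 trials per cell. Loss depends on the change from baseline to week 8. The column headings give the loss in the worse and better halves, which average 20%; in the first three columns control loss is a random 20%. Entries are the bias of the week-40 regression.

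| Correlations (0–8, 0–40, 8–40) | 30%/10%, exp. only | 35%/5%, exp. only | 40%/0%, exp. only | 35%/5%, both arms |
|---|---|---|---|---|
| 0.5, 0.5, 0.5 | 0.027 | 0.039 | 0.054 | 0.001 |
| 0.7, 0.7, 0.7 | 0.028 | 0.035 | 0.060 | 0.000 |
| 0.85, 0.85, 0.85 | 0.023 | 0.035 | 0.043 | 0.001 |
| 0.6, 0.5, 0.7 | 0.043 | 0.062 | 0.090 | 0.001 |
| 0.7, 0.6, 0.8 | 0.047 | 0.078 | 0.101 | −0.001 |

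The estimate using week 8 stays within 0.01 of zero in every cell. Where loss is random or equal in both arms, the regression's SD is about 1 to 5% larger. A corner case (correlations 0.5, 0.5 and 0.85, loss 40%/0%) goes a little beyond the table, to about 0.12.

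**6. Scale.** The largest tabulated bias, 0.101, occurs with an SD of 0.238: 0.101/0.238 = 0.42 of a standard error.

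**The case against.** **The article does not say that people missing at week 40 are dropped.** This stands. A reader might infer it, or infer that visits are pooled as if independent, but the text fixes neither the outcome visit nor the missing-data rule. Imputation from week 8 followed by linear regression fits the wording, and such detail may sit in the full protocol or analysis plan. Silence on missing data is therefore not the point. The point is that the method actually named, for outcomes with two follow-ups, does not by itself use the first.

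**A reader might also infer that the stated intention-to-treat analysis is not delivered.** The documents do not support that. The statement concerns people who stop the intervention but keep attending, and a regression by allocated arm includes them as randomised. Loss of outcome data is a separate problem.

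**Stopping the exercises is not leaving the study.** This is also correct, and the request to keep attending should reduce selective loss. It cannot guarantee attendance at week 40. Nothing in the article shows how strong the selection would be, so the bias figures are conditional on assumed scenarios.

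**The bias should not be read as a share of 0.25 SD.** That benchmark is set for BMD change ("a sample size of 46 will allow us to comment on whether a standardised effect size for the change in BMD of 0.25"). BMD has no week-8 measurement and is unaffected; no target effect is stated for balance or falls risk.

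**Conclusion.** The point holds as an improvement to a stated method, not as a contradiction in the plan. For balance and falls risk, linear regression without imputation leaves the week-8 data of people lost before week 40 unused. The week-40 contrast is then open to a bias of roughly 0.02 to 0.10 SD, provided that loss depends on week-8 status in the experimental arm only and visit correlations lie between about 0.5 and 0.85. With random loss, or equal dependence in both arms, the bias is about zero and the remaining cost is an SD about 1 to 5% larger. Even the upper end is under half a standard error. These are secondary estimates in a pilot: neither the target of 58 nor the primary feasibility and tolerance conclusions change.

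**What to change.** In Data management and analyses, separate the outcomes by number of follow-up visits.

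- **Outcomes measured at three visits:** use a linear mixed model for repeated measures. The outcomes are the week-8 and week-40 values; the terms are arm, visit, arm-by-visit, baseline value and the two stratification factors, with unstructured within-person covariance. Include every randomised participant with any follow-up visit and report the week-40 arm contrast with its CI. Multiple imputation using week-8 values, followed by the regression already named, is an acceptable equivalent.
- **BMD:** keep linear regression, since there is only one follow-up.

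The cost is a short change to the text and slightly more analysis work, with no new data. Either option assumes that values are missing at random given baseline and week 8. If loss depends on what happens after week 8, some bias remains.
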